# Using mHealth to improve adherence and reduce blood pressure in individuals with hypertension and bipolar disorder (iTAB-CV): study protocol for a 2-stage randomized clinical trial

**DOI:** 10.1186/s13063-022-06449-9

**Published:** 2022-06-29

**Keywords:** Medication adherence, Hypertension, Bipolar disorder, Mobile intervention, Text messaging, Habit formation, Antihypertensives, Blood pressure

## Abstract

**Background:**

Cardiovascular disease in individuals with mental health conditions such as bipolar disorder is highly prevalent and often poorly managed. Individuals with bipolar disorder face significant medication adherence barriers, especially when they are prescribed multiple medications for other health conditions including hypertension. Poor adherence puts them at a disproportionate risk for poor health outcomes. As such, there is a need for effective interventions to improve hypertension medication adherence, particularly in patients that struggle with adherence due to mental health comorbidity.

**Methods:**

This 5-year project uses a 2-stage randomized controlled trial design to evaluate a brief, practical adherence intervention delivered via interactive text messaging (iTAB-CV) along with self-monitoring of medication taking, mood, and home blood pressure (*N* = 100) compared to self-monitoring alone (*N* = 100). Prior to randomization, all participants will view an educational video that emphasizes the importance of medication for the treatment of hypertension and bipolar disorder. Those randomized to the texting intervention will receive daily text messages with predetermined content to address 11 salient domains as well as targeted customized messages for 2 months. This group will then be re-randomized to receive either a high (gradual taper from daily to weekly texts) or low booster (weekly texts) phase for an additional 2 months. All participants will be monitored for 52 weeks. The primary outcomes are systolic blood pressure and adherence to antihypertensive medication as determined by a self-reported questionnaire and validated with an automated pill-monitoring device. Secondary outcomes include adherence to bipolar disorder medications, psychiatric symptoms, health status, self-efficacy for medication-taking behavior, illness beliefs, medication attitudes, and habit strength.

**Discussion:**

This study specifically targets blood pressure and mental health symptom control in people with bipolar and includes implementation elements in the study design intended to inform future scale-up. Promising pilot data and a theoretical model, which views sustained medication-taking behavior in the context of habit formation, suggests that this remotely delivered intervention may help advance care for this high-risk population and is amenable to both scale up and easy adaptation for other groups with poor medication adherence.

**Trial registration:**

The study was registered at ClinicalTrials.gov (NCT04675593) on December 19, 2020.

**Supplementary Information:**

The online version contains supplementary material available at 10.1186/s13063-022-06449-9.

## Introduction

### Background and rationale

Cardiovascular (CV) disease in individuals with mental health conditions such as bipolar disorder (BD) is highly prevalent and often poorly managed [1]. Improving adherence to medications that reduce CV risk in individuals with BD is of critical public health importance [2]. A practical, technology-facilitated and patient-centered adherence intervention has the potential to improve adherence to antihypertensive medications and reduce systolic blood pressure (SBP) in poorly adherent individuals with BD and hypertension (HTN).

BD is a chronic mental health condition that affects approximately 2% of the population and which causes substantial medical, psychiatric, and financial burden [3–6]. In 2015, total economic burden of BD in the USA was estimated at $202.1 billion, corresponding to an average of $81,559 per individual/year [7]. In spite of spending more for their care, individuals with BD have a life expectancy that is shortened by 10–30 years [1, 8–11] with CV disease being the leading cause of death [12]. Between 25 and 45% of those with BD suffer from HTN [13] and non-adherence to antihypertensives, estimated to occur in 50–80% of patients [14, 15], is a significant risk of acute CV events.

Improved blood pressure control with antihypertensive drug therapy has led to dramatic improvements in US national rates of events such as heart attack and stroke [16–19]. However, individuals with BD have multiple adherence barriers that prevent them from getting the maximum benefit from available treatments. Barriers include negative attitudes about medications, lack of information, forgetting, poor organization, ineffective routines, substance use, and low self-efficacy for medication-taking behavior [20–23]. Primary care clinicians may find HTN management of patients with BD challenging given their trouble using standard medical systems appropriately with high no-show rates for medical appointments and inappropriate reliance on crisis-based care.

The Systolic Blood Pressure Intervention Trial (SPRINT), a large and rigorous longitudinal study, contributed to a change in treatment guidelines for HTN by the American Heart Association (AHA) and American College of Cardiology [24]. SPRINT showed that a treatment strategy designed to lower systolic blood pressure to less than 120 mm Hg was associated with lowering the risk of CV events by 25% and overall mortality by 27% compared to standard care with a target SBP of 140 mmHg [25]. Reaching this lower target required an average of 3.0 antihypertensive medications compared to 1.9 medications for the standard care group [25].

Medication treatment regimen complexity, including polypharmacy, is a risk factor for non-adherence and may be even more salient for individuals with BD who are likely to be on multiple medications [21, 26–28]. Polypharmacy is associated with worse adherence in treatment-resistant hypertensive patients [29]. In a large retrospective study, 42% of a hypertensive cohort that started out medication adherent became poorly adherent (defined as taking less than 80% of prescribed medications) during a 52-week follow-up period. In this same study, reduced adherence to diuretics was the most common pattern identified [29]. Studies suggest that those who need the most aggressive antihypertensive treatment become increasingly less adherent over time [30].

There is a need for practical and effective interventions to improve HTN medication adherence, particularly in patients that face challenges to their medication adherence due to mental health comorbidity. Two recent reviews of adherence interventions indicate that there is no single intervention that has strong evidence for improving antihypertensive drug adherence [31, 32]. For many patients, poor adherence is a matter of “can’t” rather than “won’t” due to forgetting to take medications or having lifestyles that make it hard to incorporate medication-taking into daily routines. Prospective memory, or the ability to remember to engage in a behavior in the future, tends to be impaired in those with BD due to executive functioning deficits such as planning and cognitive flexibility [33–35]. Thus, even when an individual has the intention to take medication, they may lack the planning or organizational abilities to do so consistently [34]. The literature indicates that forgetfulness and lack of routines is the most important reason for non-adherence [36]. Furthermore, for individuals with BD, medication regimens may be relatively complex, involving treatments for HTN as well as mood stabilizing or antidepressant drugs. Yet, there are few effective interventions to enhance adherence and improve outcomes in BD [21, 32] and those that do exist do not simultaneously target non-psychotropic non-adherence.

In summary, despite strong evidence for antihypertensive medications in reducing CV risk on a population level, adherence remains poor for many individuals, especially in people with mental illnesses such as BD. An effective adherence enhancement approach for patients with BD needs to (1) take into account the need for multiple medications, (2) address the additional adherence challenges that exist such as difficulty in planning ahead and in establishing stable healthcare routines, and (3) simultaneously target non-psychotropic and psychotropic medication adherence. Approaches that are brief, practical, and which can be embedded into standard medical care settings are of substantial public health significance as they can improve outcomes for high-risk patients and may serve as a template to improving antihypertensive adherence in other challenging patient sub-groups.

### Trial design

This 5-year project uses a 2-stage parallel group, two-arm, superiority randomized controlled trial (RCT) design with a 1:1 allocation ratio to evaluate a brief, practical adherence intervention called Individualized Texting for Adherence Building – Cardiovascular (iTAB-CV), delivered via interactive text messaging, along with self-monitoring (SM) compared to SM alone. The underlying premise is that improving adherence to antihypertensives in BD is likely to be an efficient path to improving health outcomes in a vulnerable population. The intervention is suitable for primary care or mental health settings and has potential for broad scale-up. Findings on the relationship between habit strength, medication attitudes, mood, and adherence in this project will be generalizable to other populations.

In considering the appropriate comparator to iTAB-CV in this efficacy trial, based on Mohr et al.’s seminal paper on the selection of a control condition for RCTs [37], SM will be composed of monitoring pills, blood pressure (BP), and mood as it is generalizable to standard clinical care. Each of these elements has been shown to have some efficacy in lowering SBP [38] and would allow us to determine whether iTAB-CV is efficacious above and beyond improvement yielded from implemented current clinical recommendations. The SM process for all participants involves instructing them to monitor their medication taking using an automated pill-monitoring device, take their BP weekly with a home BP monitor, and rate their mood weekly in response to a text reminder.

## Objectives

This study has four specific aims: (1) to test the efficacy of iTAB-CV + SM compared to SM alone to improve medication adherence using a RCT design, (2) to test the efficacy of iTAB-CV + SM compared to SM alone to lower SBP, (3) to explore outcomes as a function of high vs. low booster intensity compared to SM alone at 6 months (2 months post-intervention) to inform future tailoring, and (4) to explore factors that impact adherence decay between iTAB-CV + SM vs SM alone at 9 and 12 months.

Exploratory analyses will capture whether frequency of texts, depression, engagement, medication attitudes, and self-efficacy serve as moderators of longer-term outcome (6 months). Findings from this data will inform future patient-centered refinements to the intervention delivery format that will match intervention content and frequency to patient needs. Analyses will investigate the trajectory of outcomes once iTAB-CV is discontinued and whether those randomized to iTAB-CV + SM maintain better medication adherence and lower SBP compared to SM alone at 9 and 12 months.

Additional exploratory mediation analysis of adherence will include habit strength as a mediator and identification of variables that enhance (i.e., greater care engagement) or impede (i.e., depression or other psychiatric symptoms) adherence. Exploratory analysis will help characterize non-responders and determine needed adaptive modifications in frequency and length of treatment. To enhance future implementation efforts, the project will be informed by input from an advisory board made up of key stakeholders including patients, family members, providers, and administrative staff who can help inform how the intervention might fit into existing clinical workflows.

## Methods

The study methods follow the SPIRIT reporting guidelines [39] and are verified with a completed SPIRIT checklist.

### Participants

Because many individuals with BD tend to rely on public-sector care, recruitment will target diverse locations including the community, an academic medical center, local primary care settings that provide care to individuals of limited resources, and community mental health clinics. The research team will network with key representatives, such as staff from federally qualified health centers in the region, community centers, and local community mental health clinics to obtain appropriate referrals and recruit through advertising as approved by the Institutional Review Board (IRB). Electronic health records at University Hospitals will also be queried to determine a list of potential participants, who will be contacted by opt-out letters and follow-up phone calls. Pilot data suggest that a substantial proportion of participants will be minorities. Research coordinators will consent and enroll up to 200 RCT participants at an academic medical center in an urban setting and up to 12 stakeholder advisory board (SAB) members for a total of 212 participants. It is expected that most of the patient SAB members will be referred from clinicians both at the academic medical center in an urban setting as well as other local organizations serving persons with these health conditions.

Participants will have a self- or clinician-reported diagnosis of HTN, have a clinical diagnosis of BD determined at screening, be at least 21 years of age, be less than 80% adherent with their HTN medicine, and be able to provide written informed consent and participate in study procedures. Along with non-adherence, participants must have an average elevated SBP defined as at least 130 mmHg at the time of screening. Participants must also have cellular phone with texting capabilities in order to receive the intervention. Individuals at high immediate risk for suicide, those who are monolingual and non-English speaking, and individuals with an upper arm circumference greater than 50 cm will be excluded. The rationale for the latter exclusion stems from the absence of validated home blood pressure monitors for individuals with an upper arm circumference greater than 50 cm. All study participants will continue to receive services with their regular medical clinicians and providers at all sites.

As seen in Fig. 1, the entire observation duration will be 12 months. In stage 1, after consenting and passing screen, participants will receive and be trained on the use of an automated pill-monitoring device called eCAP™ (manufactured by Information Mediary Corporation, Ottawa, ON, Canada) to track use of their antihypertensive medication. Participants will use the eCAP™ for 2 months until coming in for their baseline assessment. At that time, they will be randomized on a 1:1 basis to participate in either iTAB-CV + SM or SM alone. Both interventions will be provided for 2 months with an interim phone assessment for adherence. At the end of this 2 month stage, participants will come in for an in-person assessment.

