### Equipment and devices

All participants will receive a home BP monitor at screening and undergo training on its use by study staff based on a protocol provided by the British Hypertension Society (BHS) and the National Institute for Health Research [40]. They will also receive written information including a description and pictorial presentation of how to take and record BP readings. The monitors used in this study are the Omron® 3 Series BP7100 monitors and the Omron® 7 Series Wrist BP6350 monitors for those whose arms cannot fit a standard arm cuff (manufactured by Omron Corporation, Shimogyo-ku, Kyoto, Japan). Both models are validated and approved for home use [41], and both have a memory function to record and display several recent BP readings.

All participants will have remotely administered pill monitoring via the eCAP™ which records pill bottle openings to a secure, cloud-based database. Pill bottles equipped with eCAPs™ are capable of storing a 90-day supply of one medication. Once the eCAP™ is activated by the Certiscan® Secure Reader, the eCAPs™ record each time they are opened. The data are uploaded to the cloud remotely by scanning the eCAP™ via an app on the participant’s personal smartphone or by using the Certiscan® Secure Reader. The eCAP™ will be distributed to participants when they meet all inclusion criteria for enrollment. The measurement of adherence following the introduction of electronic pill monitoring has been shown to influence medication adherence (Hawthorne effect) initially [42]. In the pilot study, adherence improved in the 4 week period between screen and baseline. Therefore, the pre-intervention phase will be extended to 8 weeks during which both treatment arms will just be monitored via eCAP™. It is anticipated that 4 weeks is long enough for return to regular medication taking behavior, so the past month and past week adherence will be gathered from the second month. Participants are incentivized to return the eCAP™ at the end of their study participation.

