**Secondary outcomes**										
Mood stabilizer adherence	TRQ	REDCap	X	X	X	X	X	X	X	X
Psychiatric symptoms	BPRS	REDCap		X		X		X		X
	MADRS	REDCap	X	X		X		X		X
Self-efficacy for medication taking	MASES-R	REDCap		X		X		X		X
Medication attitudes	BMQ	REDCap		X		X		X		X
	AMSQ	REDCap		X		X		X		X
Habit strength	SRHI	REDCap		X		X		X		X

*BL* baseline

V1 = 3 months

V2 = 4 months

V3 = 5 months

V4 = 6 months

V5 = 9 months

V6 = 12 months

The primary outcomes are SBP and adherence with antihypertensive medication. While SBP is the primary outcome for this analysis, both SBP and diastolic BP will be measured. A recently published joint Policy Statement from the AHA and American Medical Association recommend home-based BP monitoring for the most accurate assessment to minimize biased/artifact findings and yield the most valid results [51]. The joint statement states, “BP may differ considerably when measured in the office and when measured outside of the office setting, and higher out-of-office BP is associated with increased CV risk independent of office BP. Self-measured BP monitoring, the measurement of BP by an individual outside of the office at home, is a validated approach for out-of-office BP measurement. Several national and international HTN guidelines endorse self-measured BP monitoring.” In addition to optimizing accuracy, use of home-based BP evaluation will minimize potential COVID-19 exposure for study participants, most of whom are adults with multiple chronic health conditions.

At screening, participants will be trained on the use of the BP monitor following the BHS protocol [40]. Participants will be asked to take their own BP 2 times consecutively with 1 minute in between each reading and after sitting in a chair quietly for 5 min. BP readings will be collected twice a day, in the morning and evening, for 3 to 7 days while a member of the study staff observes the participant over a video platform, in person, or over the phone. Alternately, the participant can send a screen shot of the BP readings via text to study staff. Once they have obtained 12 readings total (6 in the AM and 6 in the PM), SBP will be averaged across all readings. Participants will also use these procedures to ascertain BP readings at follow-up time points. The interim BP readings will be conducted in real-time using the remote platform or by phone in real time, or if needed, will be measured beforehand and reported during the visit.

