### Data analysis plan

For the primary intent-to-treat analyses (aims 1 and 2), linear mixed effects longitudinal analysis of adherence (TRQ past month is primary) and SBP to 4 months (V2) will be conducted. A treatment variable will be included to indicate randomization to either iTAB-CV + SM or SM alone. Secondarily, we will also consider models with longer-term outcomes. Within the longitudinal models, significant interaction of the treatment variable with time indicates that the treatments have a different course of response. The researchers will first fit models with time as a covariate and, alternatively, consider time period as a categorical variable. Time by treatment interaction will be of primary inferential interest. To account for possible imbalances across treatment groups and other sources of variation, explanatory variables such as gender, ethnicity, and BD diagnosis type (I vs. II) will be considered for inclusion in the mixed models.

Researchers will consider representing TRQ scores as binary outcomes, indicating whether or not an adherence threshold has been met (e.g., 80% adherent). Researchers will thus also consider generalized linear mixed models for binary outcomes (SAS PROC GLIMMIX), as well as fitting a longitudinal model on the difference values with baseline value adjustment. Graphical methods will be used extensively to examine distributions of residuals, identify potentially influential points, and guide data transformations to better approximate normality if warranted. Sensitivity analysis of results will be conducted by modeling a range of plausible correlation structures.

In secondary analyses for both aims 1 and 2, follow-up at 6 and 12 months (V4 to V6) will also be compared in the respective longitudinal analyses for adherence and SBP. The researchers will conduct contrast analyses of treatment by (discrete) time interaction at time periods V4 and V6 and differences from baseline in treatment dose-level subgroups (higher versus lower booster levels) at V4 and V6 using two sample *t*-tests or nonparametric Mann-Whitney tests. Additionally, the researchers will compare corresponding TRQ and eCAP™ adherence levels. Correlation between the measures will be estimated and Bland-Altman plots will be generated [67].

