### Sample size calculations

Power analyses are based on computations from the Repeated Measures and Sample Size (RMASS) [72] with inputs estimated from prior study data. Our projected sample size is *n* = 200, with 100 participants per arm. In this power analysis, the research team will assume type I error levels of 0.025 for each of the two primary analyses, using Bonferroni correction to account for multiple comparisons. Conservatively, for this study, the researchers will assume 25% attrition based on a previous 12 month trial conducted by members of the study team with individuals with comorbid serious mental illness and diabetes [73]. For sample size requirement for aim 1, the investigators used past-month TRQ as an approximation of expected and longer-term maintenance adherence status and considered primary outcomes to be at 3 months. The investigators expect similar or even greater effect sizes at 4 months given the longer treatment duration. In the pilot study, there was 23.10% improvement in TRQ observed for iTAB-CV. The control comparator for the efficacy trial will be SM of adherence, BP, and mood. Based on the literature, no improvement in self-reported adherence was reported in a similar control arm [74]. The study staff thus assume no change in adherence. In a BD adherence RCT, 7% improvement was observed in the control arm. Hence, the investigators conservatively project a 7% mean improvement in adherence among controls. Thus, (1) there is a mean difference of 16.1% in adherence after 4 months between arms and (2) suppose autoregressive (AR(1)) model covariance structure with correlation coefficient of 0.44 and an error variance of 308, as estimated value from the data. With assumed attrition of 25%, for a 2-sided test of the treatment by time interaction effect being equal to zero, and with alpha = 0.025 and power = 0.80, the required total sample size is approximately 78.

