From the pilot data, mean screen SBP was 144.81 (SD 15.46). Change from screen to 3 months with the iTAB-CV intervention saw a mean reduction in SBP of 8.78. Reductions in BP of at least 2 mmHg can significantly reduce the incidence of cardiovascular disease and its complications in both hypertensive and normotensive individuals, and reductions of the magnitude seen in this team’s pilot work is well above thresholds that are considered clinically meaningful [75]. Based on our preliminary mixed model, the researchers also observed compound symmetry correlation parameter value of 0.36. This covariance model had similar model fit as with an AR(1) model in terms of AIC/BIC criteria and parameter estimate values. The researchers will assume no SBP pressure change is observed in the SM arm and estimated error standard deviation of 15.46, as observed [38]. Finally, in a linear mixed model with participant-level random effects, with two-sided type I error of 0.025, power = 0.80 for the projected sample size of 182 participants. The study staff will target a sample of 200 for the study to allow for some deviation from assumptions. Thus, the researchers should have sufficient statistical power for the first 2 primary aims.

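### Screening SBP is a second pre-randomisation measurement for which the primary SBP analysis names no use; using it is a free but modest gain in precision, for SBP only

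*Protocol article*

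**What the plan says.** - **Two values before randomisation.** Under Participants, "participants must have an average elevated SBP defined as at least 130 mmHg at the time of screening". The text after Table 2 describes the screening procedure: "Once they have obtained 12 readings total (6 in the AM and 6 in the PM), SBP will be averaged across all readings". It adds that later readings follow the same procedure. Table 2 marks SBP at screening and at baseline. Participants (stage 1) and Assessments and outcomes place baseline, and with it randomisation, at month 2. Under Equipment and devices, "the pre-intervention phase will be extended to 8 weeks during which both treatment arms will just be monitored", so no treatment is given between the two measurements.
- **Primary analysis.** Under Data analysis plan, "linear mixed effects longitudinal analysis of adherence (TRQ past month is primary) and SBP to 4 months (V2) will be conducted". The inferential term is treatment by time, with time fitted first as a covariate and alternatively as categorical. Candidate covariates are gender, ethnicity and bipolar type. Adjustment for the baseline value appears only in an alternative model on difference values. Screening values are given no role, and the visits that enter the model are not listed.
- **SBP planning.** The sample size section says the team will "assume type I error levels of 0.025 for each of the two primary analyses", and for SBP gives "with two-sided type I error of 0.025, power = 0.80 for the projected sample size of 182 participants".

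**The concern.** Screening SBP already decides eligibility, so it exists for everyone at no extra cost, and SBP is the outcome that sets the sample size (182, against about 78 for TRQ). If the model starts at baseline, this information goes unused.

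A second point follows from the article's clock, which starts at screening: month 4 is V2, two months after randomisation. A model run to month 4 could therefore take screening in as an ordinary time point. With linear time, two untreated months would then enter the tested slope. One sentence on the role of screening SBP would settle both points.

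**Working it through.** **Inputs.** The SD of 15.46 and a flat control arm come from Sample size calculations: "assume no SBP pressure change is observed in the SM arm and estimated error standard deviation of 15.46". The effect of 8.78 comes from "Change from screen to 3 months with the iTAB-CV intervention saw a mean reduction in SBP of 8.78". It is a pilot change within one arm and is used here, as in the plan, as the between-arm difference d. The same section gives compound symmetry with correlation r = 0.36, two-sided alpha 0.025 (z = 2.241) and 25% attrition. Assumed here: the difference is 0 at baseline, d/2 at V1 and d at V2; 75 per arm are retained (100 × 0.75); variance is equal at all visits. Then σ² = 15.46² = 239.0.

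**The plan's figure.** A treatment-by-linear-time test on baseline, V1 and V2 with retention of 100%, 87.5% and 75% requires N = 182.5, against 182 stated. The steps below use the simpler 75 complete participants per arm.

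**Step 1: interaction test, baseline arm difference left free.** With x = months of treatment, the V2 effect is twice the slope, and under compound symmetry its variance is 4 × 2σ²(1 − r)/(n·Sxx).
- Without screening, x = 0, 1, 2 and Sxx = 2. Variance = 8 × 239.0 × 0.64/(75 × 2) = 8.16, SE 2.86. Power = Φ(8.78/2.86 − 2.241) = 0.80.
- With screening as a second zero-treatment row, x = 0, 0, 1, 2 and Sxx = 5 − 9/4 = 2.75. Variance = 5.93, SE 2.44, power 0.91.
- Reduction = 1 − 2/2.75 = 27%. The factor (1 − r) cancels, so under compound symmetry this percentage does not depend on r.

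**Step 2: baseline-adjusted model (arms equal before randomisation).** Variance = 8σ²/(n·Q), where Q = [Σx² − r(Σx)²/(1 + (T − 1)r)]/(1 − r), T is the number of visits, Σx² = 5 and (Σx)² = 9.
- T = 3: Q = (5 − 0.36 × 9/1.72)/0.64 = 4.87. Variance 5.24, SE 2.29, power 0.945.
- T = 4, with screening: Q = (5 − 0.36 × 9/2.08)/0.64 = 5.38. Variance 4.74, SE 2.18, power 0.963.
- Increment from screening: 1 − 4.74/5.24 = 9.5%. Baseline adjustment without screening already gives 1 − 5.24/8.16 = 36%.

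**Step 3: the same comparison in required N, with staggered retention.**

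| SBP model | Without screening | With screening |
|---|---|---|
| Interaction, compound symmetry 0.36 | 182.5 | 136.1 |
| Baseline-adjusted, compound symmetry 0.36 | 124.2 | 112.6 |
| Baseline-adjusted, AR(1) 0.36 per month | 141.9 | 141.9 |

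**Step 4: sensitivity (75 per arm).**
- AR(1) 0.36 per month: the interaction test gains 19% of variance (power 0.65 to 0.76); the baseline-adjusted model gains nothing and loses nothing.
- Other compound-symmetry values (assumptions): the increment beyond baseline adjustment is 4% at r = 0.2 and 14% at r = 0.5. It grows with correlation.
- Truncation: if 15.46 and 0.36 describe an unselected population with mean 130 to 144.8 mmHg (assumption), selecting screening SBP of at least 130 and simulating gives an increment of about 4 to 6%.

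**Step 5: screening entered as month 0 of a linear time axis, compound symmetry.** Times 0, 2, 3, 4 have mean 2.25 and sum of squares 8.75. The fitted slope is (0.75 × 0.5d + 1.75 × d)/8.75 = 0.243d per month. Over the two treated months that is 0.486d, or 4.3 mmHg instead of 8.78.

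**Step 6: TRQ.** Under the plan's AR(1) 0.44, variance 308 and difference 16.1, the baseline-adjusted N is 54.0 with or without screening. Power at N = 200 is above 99% even in the interaction model without screening. (The same three-visit model gives 85.5 where the plan states about 78. That gap does not affect this point.)

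**The case against.** The strongest reply is that nothing here is an error. The planned model is valid, its SBP sample size reproduces, and an article may leave its visit list to the full protocol or SAP. The 27% also depends on comparing against a model that leaves the baseline arm difference free. Baseline adjustment, which the plan already considers as an alternative, takes power to 0.945 without screening, so what screening adds is under two points of power. The plan also reports that compound symmetry and AR(1) fitted the pilot data similarly, and under AR(1) that remainder is zero. All of this stands and limits the point to an efficiency improvement.

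Four stronger readings are tempting, and the documents do not support them:
- **The plan never uses screening.** It names no use, but it neither lists nor excludes visits. The stated 182 does not settle it: some four-visit slopes that include screening give 181.1 to 183.9.
- **The SBP effect will be halved.** That needs screening to be entered and time to be linear from month 0. Neither is stated together, and categorical time with a V2-versus-baseline contrast has no such dilution.
- **Both primary outcomes lose precision.** TRQ gains nothing after baseline adjustment under the plan's own covariance. Equipment and devices also gives a reason for taking pre-intervention adherence from the second run-in month: monitoring itself changes adherence at first.
- **The low correlation of 0.36 makes a second value especially useful.** It works the other way, as Step 4 shows.

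**Conclusion.** The point holds as a no-cost improvement to the primary SBP analysis. Screening SBP is pre-randomisation information collected on everyone, and the data analysis plan gives it no role. Against the interaction test as written, using it is worth about 27% of variance (power 0.80 to 0.91), but baseline adjustment alone more than matches that. The part that belongs to screening is at most about 9.5% of variance on top of baseline adjustment (power 0.945 to 0.963), equivalent to about 20 more participants (200/0.905 = 221). It is about 4 to 6% if truncation at 130 mmHg lowers the correlation, and nil under AR(1).

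These figures rest on the plan's SD, correlation and effect, an effect that builds linearly from baseline to V2, and 75 per arm retained. The article does not say whether the SD and correlation describe a population already selected on SBP. The planned analysis is not biased so long as screening stays off a linear treatment-by-time axis.

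**What to change.** In the primary SBP model, use screening SBP together with baseline SBP as pre-randomisation information. Either of two forms will do:
- both values as covariates; or
- both visits as pre-randomisation rows, with means constrained equal across arms.

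List the visits that enter the model and state that screening is not a point on a linear treatment-by-time axis. Leave the TRQ model as it is.

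The cost is a sentence or two of analysis wording and one extra covariate or row, settled before unblinding. No new visits or data are needed. The 130 mmHg cut-off applies to both arms alike before randomisation, so it does not bias the comparison; it can only reduce the gain.
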